## Method/Design

### Study Design

Prospective, single-center, observational study.

### Study Setting

Neonatal Intensive Care Unit and Postnatal Wards, Capital Coast District Hospital Board (CCDHB), Wellington, New Zealand.

### Primary Outcome Measures

Cerebral creatine content at term CPAPlasma (bi-weekly) and urine (weekly) creatine and GAA levels from birth until hospital discharge and at CPACreatine, GAA, and amino acid levels in infant nutrition (TPN, formula, or breast milk) supplied from birth until discharge and at CPA

### Secondary Outcome Measures

Global injury score from MRI at term CPAGeneral movement assessment score at term CPA and 3 months of CPADAYC-2 assessment score at 3 months of CPA

### Study Population

#### Inclusion Criteria

Preterm infants receiving care within the Neonatal Intensive Care Unit at CCDHB or healthy term infants at 39–40 weeks’ gestation from low-risk pregnancies delivered at CCDHB.

#### Exclusion Criteria

Babies with major congenital, genetic, or chromosomal abnormalities known to affect neurodevelopmental outcomesHypoxic ischemic encephalopathyInborn (proven or suspected) errors of metabolismFetal growth restriction (birth weight < 10th percentile on customized percentiles)

### Recruitment

We will recruit infants at gestational ages 23^+0^–26^+6^, 27^+0^–29^+6^, 30^+0^–32^+6^, 33^+0^–36^+6^, and 39^+0^–40^+6^ weeks. We will aim to capture 20 infants at each time point (with equal numbers of males and females). Eligible infants will be identified based on gestational age at delivery and consideration of inclusion and exclusion criteria. Pregnant women will be approached at presentation to Delivery Suite to discuss study participation. If consent is obtained, the mother and infant will be recruited to the study and the consulting obstetric, midwifery, neonatal, and nursing team advised of their involvement. Where pre-delivery consent is not obtained due to rapidity of labor and/or other clinical factors, cord blood will be collected preemptively, and retrospective consent and maternal blood sample sought within 24 h of delivery. If the parents do not wish to participate, the cord blood sample will be disposed of using routine clinical biological waste disposal systems and no further study samples collected.

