### Sample Size

This study will be the first observational study of creatine homeostasis in the preterm infant that encompasses plasma, urine, nutrition, and cerebral creatine measures across time. As the outcomes are mainly descriptive, no formal power calculation has been performed. However, ^1^H-MRS results reported by Koob et al. (2016) showed comparison of 13 preterm vs term infants allowed for measurement of a statistically significant (−17%) reduction in cerebral creatine content in preterm infants at CPA (tCr/H_2_0 × 10^−3^; term 0.12 ± 0.1 vs preterm 0.10 ± 0.1). This same study had a 20–25% failure rate in obtaining accurate MRI/^1^H-MRS measurements at CPA (Koob et al., 2016). Taking these data into consideration and a potential loss to follow-up at 3-month of 20%, we aim to capture 20 infants in each gestational group.

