### Statistical Analysis

Characteristics of the population will be tabulated, along with appropriate descriptive statistics of the study sample. Continuous data will be assessed for normality and expressed as means and standard deviations or median and interquartile range as appropriate. Categorical data will be expressed as counts and proportions. Average creatine content from nutrition per week for each baby in the early postnatal period will be calculated.

Differences in creatine and GAA measures (^1^H-MRS, plasma or urine) between infants born preterm and those born at term will be assessed at CPA using a t-test or Mann-Whitney U test as appropriate. The correlation between gestational age at birth and creatine and GAA measures at CPA will also be determined using a Spearman or Pearson correlation. Preterm infant plasma and urine creatine and GAA concentrations and creatine:GAA ratio in the early postnatal period will be described and plotted. Associations between cerebral creatine content, plasma and urine creatine concentrations with maternal, and infant characteristics at CPA will be determined using Spearman or Pearson correlations for continuous data (maternal age, gestational age, birth weight, parity, gravity, placental weight) or a t-test or Mann-Whitney U test for categorical data (infant sex, mode of delivery, maternal comorbidities, country of birth, ethnicity, and dietary preferences), as appropriate. Differences in creatine, GAA, and amino acid content of nutrition sources (TNP, formula or breast milk) will be determined using a one-way ANOVA or Kruskal-Wallis H test as appropriate. The association between creatine, GAA, and amino acid content of nutrition sources (TNP, formula or breast milk) and infant plasma and urine creatine at CPA will be assessed using a Spearman or Pearson correlation as appropriate. Finally, the association between cerebral creatine content, plasma creatine levels, and the ratio of plasma:cerebral creatine at CPA with GMA, MRI global injury, and DAYC-2 scores will be determined using linear regression at both CPA and at 3 months’ corrected postnatal age. Potential confounders such as gestational age and maternal and infant characteristics will be assessed, along with collinearity, prior to performing multivariable linear regression.

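### Multiple births are not excluded or limited to one infant per mother, and every named test assumes independent infants; if siblings enrol, maternal-characteristic and gestational-age associations get standard errors that are modestly too small

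*Protocol article*

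**What the plan says.** **Eligibility.** The Inclusion Criteria admit "Preterm infants receiving care within the Neonatal Intensive Care Unit at CCDHB" and, for the reference group, healthy term infants "from low-risk pregnancies delivered at CCDHB". The four Exclusion Criteria cover congenital, genetic or chromosomal abnormality, hypoxic ischemic encephalopathy, errors of metabolism and growth restriction. None concerns plurality.

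**Unit of counting.** Recruitment states: "We will aim to capture 20 infants at each time point (with equal numbers of males and females". With four preterm groups and one term group this makes 80 preterm and 20 term infants.

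**Data collected.** Monitoring and Data Collection lists IVF among the maternal factors. Plurality is in neither the maternal nor the infant list.

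**Analysis.** Statistical Analysis names these methods:
- Preterm–term differences in creatine and GAA "will be assessed at CPA using a t-test or Mann-Whitney U test as appropriate".
- Continuous maternal and infant characteristics by "Spearman or Pearson correlations for continuous data (maternal age, gestational age, birth weight, parity, gravity, placental weight"), and categorical ones by t-test or Mann-Whitney.
- Neurological outcomes, whose associations with creatine "will be determined using linear regression at both CPA and at 3 months" of corrected age.
- Adjustment: "Potential confounders such as gestational age and maternal and infant characteristics will be assessed, along with collinearity, prior to performing multivariable linear regression".

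No mother-level term, clustered variance or rule for selecting one sibling is named.

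**The concern.** Twins or triplets share a mother and, ordinarily, a gestational age, so a sibling set falls in one gestational group and fills two or three of its 20 places. Each named method takes its standard error from the number of infants.

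The problem is sharpest where the predictor is constant within a sibling set: maternal age, parity, gravity, gestational age, maternal diet, country of birth and comorbidities. One mother's value then enters two or three times, while the siblings' creatine values are likely to resemble each other. The adjustment step deals with confounding and collinearity and does nothing about correlation within a family.

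At stake is the stated precision of the associations with maternal and infant characteristics (the third specific aim) and of the correlation with gestational age. The Discussion intends the data to supply effect sizes for later studies, so precision that is too optimistic would carry forward.

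**Working it through.** **1. The plan's own figure.** Sample Size says that "no formal power calculation has been performed". It refers to an earlier spectroscopy study with 13 preterm infants, a 20–25% scan failure rate, and a possible 20% loss at 3 months. The article gives no formula, but inflating 13 for both losses comes close to 20:
- 13 / 0.80 / 0.80 = 20.3
- 13 / 0.75 / 0.80 = 21.7

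Nothing in this allows for siblings.

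**2. Inputs that the documents do not give.** Let f be the share of preterm infants who are in twin pairs and ρ the within-pair correlation of the outcome. Assumed ranges: f = 0.10–0.40 and ρ = 0.3–0.8. No significance level is stated; two-sided 0.05 is assumed. Term infants are assumed to be singletons.

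**3. Predictor identical within a pair, preterm infants only.** Design effect DE = 1 + fρ. Actual error = 2 × [1 − Φ(1.96 / √DE)].

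| f | ρ | DE | 20 infants are worth | Actual error |
|---|---|---|---|---|
| 0.10 | 0.3 | 1.03 | 19.4 | 5.35% |
| 0.30 | 0.5 | 1.15 | 17.4 | 6.8% |
| 0.40 | 0.8 | 1.32 | 15.2 | 8.8% |

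The true standard error is √DE = 1.015 to 1.149 times the naive one. A simulation of 8,000 runs at f = 0.30, ρ = 0.5 gave 7.1% for a Pearson correlation with a mother-level covariate, against 6.8% by formula.

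In mothers, a group of 20 has one pair and 19 mothers at f = 0.10, and four pairs and 16 mothers at f = 0.40.

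**4. Term infants included.** The plan does not restrict these associations to preterm infants. With 20 singletons among 100 infants, f becomes 0.8f, so DE = 1 + 0.8fρ:
- Low end: 1 + 0.8 × 0.10 × 0.3 = 1.024, error 5.3%.
- High end: 1 + 0.8 × 0.40 × 0.8 = 1.256, error 8.0%.

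**5. Cerebral creatine, with scan failure.** A pair contributes correlation only if both siblings have usable spectra. With failure of 20–25%, taken as independent between siblings, f shrinks by a further factor of 0.80 to 0.75:
- Low end: 1 + 0.8 × 0.75 × 0.10 × 0.3 = 1.018, error 5.2%.
- High end: 1 + 0.8 × 0.80 × 0.40 × 0.8 = 1.205, error 7.4%.

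**6. Pooled preterm–term test, 80 against 20.** The naive variance is proportional to 1/80 + 1/20 and the true variance to DE/80 + 1/20. The ratio is (DE + 4)/5:
- Low end: 5.03/5 = 1.006, error 5.1%.
- High end: 5.32/5 = 1.064, error 5.7%.

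The 20 term infants dominate this variance. The simulation at f = 0.30, ρ = 0.5 gave 5.5%.

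**The case against.** **The article is condensed and silent on multiples.** It never mentions twins, and its operational text speaks of one mother and one infant. A full protocol or analysis plan could hold a sibling rule. This stands so far as enrolment of siblings is inferred from open criteria and is not stated. It does not remove the point: the article does fix open eligibility, a target counted in infants, and a named test for each analysis, and these do not fit together once a sibling pair is enrolled.

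**The size is assumed.** This stands. At the low end of the ranges the effect is negligible. The growth-restriction exclusion may remove some siblings, and part of the sibling correlation would be explained by gestational age and maternal covariates in the multivariable models.

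**The study is mainly descriptive.** This also stands. No power or significance level is stated, so none is invalidated, and the Discussion already concedes that sample size may limit some analyses.

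A reader might infer three stronger things that the documents do not support:
- *That siblings are double-counted throughout.* Only predictors shared by siblings are repeated. Creatine outcomes are measured on each infant and are correlated, not duplicated.
- *That sibling correlation cannot be handled because plurality is not recorded.* Mothers are recruited with their infants, give their own blood sample and have their own data recorded, so sibling sets can be identified. Clustering needs a mother identifier, not a plurality field.
- *That plurality is a separate confounding error in the preterm–term comparison.* The term group is low-risk by design and may differ in many pregnancy factors. Plurality would be one of them.

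**Conclusion.** The point holds as a modest one. If siblings are enrolled and the tests are run as named, standard errors for associations with maternal characteristics and gestational age are too small. Under the assumed ranges (10–40% of preterm infants in twin pairs, correlation 0.3–0.8), a nominal 5% test runs at about 5.35–8.8% in preterm infants. That becomes about 5.3–8.0% with the term group included and about 5.2–7.4% for cerebral creatine after scan failures. Predictors that differ between siblings, such as infant sex and birth weight, are generally less affected.

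It would be wrong to read this as undermining the main preterm–term comparison, where the error stays at about 5.1–5.7%, or the target of 20 per group, which rests on no formal power calculation.

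**What to change.** Keep all siblings, and state in the analysis section that infants are nested within mothers. Use the existing mother–infant link to apply mother-clustered standard errors, or GEE with the mother as cluster, in the infant-level comparisons, correlations and regressions. Apply this to the pooled data. Within a single group of 20 the assumed range gives only one to four pairs, too few to estimate a mother-level component reliably.

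Add plurality to the data collected, and report the number of mothers beside the number of infants in each group. An analysis with one randomly chosen infant per mother is a simple alternative and can serve as a sensitivity analysis.

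The cost is a sentence or two in the analysis section, one data field and slightly wider intervals. Keeping all siblings does not slow recruitment.

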### Sample and Data Collection

#### Blood, Urine, and Nutrition Sampling

A schematic overview of the sampling regime for each participant is outlined in Figure 1. At the time of birth, we will use a finger prick to collect ~120 μl of maternal whole blood using a capillary tube. A 2-ml venous cord blood sample will also be collected from which a ~120 μl sample will be obtained using a capillary tube. Then, while infants are receiving care in the NICU, or on postnatal wards, and at follow-up appointments, the following samples will be collected. Sample frequency will be dictated by gestational age at birth.

**Figure 1 fig1:**
[figure not shown]
Schematic representation of UNICORN sampling regime. Samples of neonatal blood, urine, and nutrition will be collected weekly or bi-weekly for the duration of the infants stay in hospital. Magnetic resonance imaging (MRI) and magnetic resonance spectroscopy (^1^H-MRS) will be performed at term corrected postnatal age (CPA). Infants will also undergo a general movements assessment (GMA) at CPA and at 3 months CPA. At the follow-up appointment at 3 months CPA, further neurological assessment will be completed using the Developmental Assessment of Young Children – Second Edition (DAYC-2) assessment tool.

**Blood sampling**: A blood sample will be collected biweekly. We will perform a heel prick to collect ~120 μl of whole blood using a capillary tube. All blood samples (cord, maternal, or infant) will be transferred to a Hemaspot™ SE blood separation device to facilitate collection of the cell-free blood fraction (referred to throughout as plasma for clarity) from a small volume of whole blood. Hemaspots are allowed to dry at room temperature before being stored at −20°C for future analysis.

**Urine sampling**: Around the same time as the blood collection, and on each alternate week, we will place some gauze into the infant’s nappy to facilitate a spot urine collection. Once obtained, this sample will be transferred to an Eppendorf tube and stored at −80°C for future analysis.

**Nutrition sampling**: A 200 μl sample of the nutrition (TNP, formula, and breast milk) being fed to each infant at the time of the blood and urine sampling will be collected. If in powdered form (formula), this will be reconstituted following standard practices. All samples will be transferred into an Eppendorf tube and stored at −80°C for future analysis.

### Monitoring and Data Collection

The following covariates/potential confounders will be collected as part of this study:

Maternal characteristics and birth outcomes data:

Maternal ageComorbidities/factors (preeclampsia, gestational diabetes, chorioamnionitis, IVF)Country of birthDietary preferences (omnivorous, vegetarian, vegan)Smoking statusParityGravityMode of deliveryPlacental weight

Infant characteristics:

Gestational ageSexBirth weightEthnicityWeight and corrected postnatal age at the time of each sample collectionPresence of postnatal infection (blood culture positive and/or treatment with systemic antibiotics for >24 h) or necrotizing enterocolitis (Modified Bells Classification Grade II-III determined by the treating Pediatric Surgeon at time of diagnosis).Feeding schedule prior to each sample collection (<24 h)Venous hemoglobin and hematocrit count prior to blood sample collection

#### MRI/^1^H-MRS Data Acquisition

At 40 weeks of corrected postnatal age (CPA), each participant will undergo a MRI/^1^H-MRS scan. MR examinations will be performed on a Siemens 3T Skyra using a 16-channel dedicated pediatric head coil. Infants will be examined without sedation using a “feed and wrap” technique according to standard institutional practice. In brief, infants are brought to the MRI unit, fed, and swaddled comfortably while being monitored with continuous pulse oximetry before being placed in the MRI scanner. Standard, size appropriate, hearing protection will be used for all infants. Sequences will be performed to demonstrate brain anatomy and will include T1 3D 1 mm volumetric, T2 1 mm 3D volumetric scans, T2 TSE FLAIR, and T1SE MTC sequences. These sequences will also contribute to the analysis of any detected brain pathology. T2 SWI axial images will be performed to show calcification and blood products. Sequences for the detection of vascular injury and infarction will include diffusion sequences (b value = 2000), resting BOLD, and arterial spin labeling. ^1^H-MRS will provide chemical spectra of the brain to further analyze brain pathology and measurement of cerebral creatine content. For MR spectroscopy, the voxel will be placed over the white matter underlying the central sulcus within the centrum semiovale and spectra acquired with a long echo time (TE 135 ms) (Koob et al., 2016).

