## Abstract

Creatine is an essential metabolite for brain function, with a fundamental role in cellular (ATP) energy homeostasis. It is hypothesized that preterm infants will become creatine deplete in the early postnatal period, due to premature delivery from a maternal source of creatine and a limited supply of creatine in newborn nutrition. This potential alteration to brain metabolism may contribute to, or compound, poor neurological outcomes in this high-risk population. Understanding Creatine for Neurological Health in Babies (UNICORN) is an observational study of circulating and cerebral creatine levels in preterm infants. We will recruit preterm infants at gestational ages 23^+0^–26^+6^, 27^+0^–29^+6^, 30^+0^–32^+6^, 33^+0^–36^+6^, and a term reference group at 39^+0^–40^+6^ weeks of gestation, with 20 infants in each gestational age group. At birth, a maternal capillary blood sample, as well as a venous cord blood sample, will be collected. For preterm infants, serial infant plasma (heel prick), urine, and nutrition samples [total parenteral nutrition (TPN), breast milk, or formula] will be collected between birth and term “due date.” Key fetomaternal information, including demographics, smoking status, and maternal diet, will also be collected. At term corrected postnatal age (CPA), each infant will undergo an MRI/^1^H-MRS scan to evaluate brain structure and measure cerebral creatine content. A general movements assessment (GMA) will also be conducted. At 3 months of CPA, infants will undergo a second GMA as well as further neurodevelopmental evaluation using the Developmental Assessment of Young Children – Second Edition (DAYC-2) assessment tool. The primary outcome measures for this study are cerebral creatine content at CPA and plasma and urine creatine and guanidinoacetate (creatine precursor) concentrations in the early postnatal period. We will also determine associations between (1) creatine levels at term CPA and neurodevelopmental outcomes (MRI, GMA, and DAY-C); (2) dietary creatine intake and circulating and cerebral creatine content; and (3) creatine levels and maternal characteristics. Novel approaches are needed to try and improve preterm-associated brain injury. Inclusion of creatine in preterm nutrition may better support *ex utero* brain development through improved cerebral cellular energy availability during a period of significant brain growth and development.

**Ethics Ref:** HDEC 18/CEN/7 New Zealand.

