*In utero* fetal magnetic resonance spectroscopy (^1^H-MRS) studies indicate cerebral creatine accretion occurs from 18 to 40 weeks of gestation (Evangelou et al., 2015). Postnatal studies have also clearly identified that an increase in cerebral creatine concentration occurs during the first 3 months of life (Blüml et al., 2012; Blüml et al., 2014). The importance of a maternal source of creatine for the developing fetus and the continued postnatal accretion of cerebral creatine is made evident by those infants diagnosed with inherited creatine deficiency syndromes. These infants typically raise no concerns antenatally; however, as postnatal creatine levels fall, they become progressively more symptomatic with altered neurological state (Almeida et al., 2006) and complex neurological symptoms including impaired psychomotor development, seizures, and cognitive impairment (Battini et al., 2006).

In adults, creatine is acquired *via* the diet and *de novo* synthesis, with each contributing ~50% (Brosnan and Brosnan, 2007). However, in infancy, due to low levels of creatine in human breast milk and commercial formulas, a term infant most likely synthesizes between 64 and 93% of their daily creatine requirements (Edison et al., 2013). The age at which a fetus/newborn develops the capacity to synthesize creatine is currently unknown, but it requires sufficient renal, hepatic, and cerebral maturity to express the enzymes necessary for creatine synthesis. Evaluation of AGAT and GAMT expression in the rat embryo found that AGAT was expressed in isolated cells of the CNS from 0.6 gestation; however, widespread expression of AGAT and rudimentary GAMT expression were not apparent before 0.8 gestation (Braissant et al., 2005). Our own studies in the precocial spiny mouse found that the fetal kidney and liver do not express AGAT and GAMT before 0.9 gestation, an age and maturation equivalent to ~35 weeks’ human gestation (Ireland et al., 2009). Taken together, these observations raise compelling questions about progressive creatine depletion in preterm infants, and whether this complication of nutritional compromise predisposes or compounds their risk of altered cerebral metabolism and thus long-term neurodevelopmental disability.

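### The preterm–term test of cerebral creatine takes no account of age at scan, although only term infants can be born too late for a 40+0 scan and creatine is said to be rising

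*Protocol article*

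**What the plan says.** The MRI/1H-MRS Data Acquisition section sets a single time point: "At 40 weeks of corrected postnatal age (CPA), each participant will undergo a MRI/^1^H-MRS scan". Other sections say only term CPA. The Abstract describes "a term reference group at 39^+0^–40^+6^ weeks of gestation, with 20 infants in each gestational age group", and Recruitment repeats the upper bands as "33^+0^–36^+6^, and 39^+0^–40^+6^ weeks".

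On the biology, the Introduction states that "cerebral creatine accretion occurs from 18 to 40 weeks of gestation" and that "an increase in cerebral creatine concentration occurs during the first 3 months of life". It gives no rate per week.

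On the analysis, the Statistical Analysis section says that preterm–term differences in creatine and GAA measures "will be assessed at CPA using a t-test or Mann-Whitney U test as appropriate". Neither test takes a covariate. Adjustment comes up only at the end of the section, after the analysis of neurological outcomes: "Potential confounders such as gestational age and maternal and infant characteristics will be assessed, along with collinearity, prior to performing multivariable linear regression". The list under Monitoring and Data Collection includes corrected age at each sample collection. It does not list age at scan separately, and no named analysis uses either.

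**The concern.** Cerebral creatine at term CPA is the first-listed primary outcome. The Discussion frames the expected finding as a contrast with infants of equal age since conception, but the stated test does not secure that contrast.

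The constraint on timing is one-sided. Every preterm infant has been born before 40+0 and can be scanned then. A term infant born at 40+1 or later cannot. If term infants are older at scan on average while creatine is rising, their mean is raised by age alone, and the comparison shifts in the direction of the study hypothesis. The Discussion says that supportive results would inform a randomized trial of supplementation, so it matters that the contrast is not partly one of age.

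**Working it through.** **Inputs from the article.** Term births from 39+0 to 40+6; scan at 40 weeks for all; 20 infants per group, four preterm groups and one term group; scan failure 20–25%; reference means 0.12 (term) and 0.10 (preterm).

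**Assumptions.** Term births are uniform by day. Creatine rises by 1–3% per week. The lag from birth to scan is 0, 7 or 14 days. None of these is in the article.

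**Reference effect.** (0.12 − 0.10)/0.12 = 16.7%, which matches the cited 17%.

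**Share born after 40+0.** Days 40+1 to 40+6 are 6 of 14, or 43%. That is 20 × 6/14 = 8.6, about 9 of the 20 term infants.

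**Mean offset (term minus preterm age at scan).**

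- A. Week 40 read as 40+0 to 40+6, each infant scanned evenly between the earliest possible day and 40+6. Preterm infants average 3.0 days past 40+0. Of the 14 term birth days, the 8 up to 40+0 also average 3.0. The 6 later ones average 3.5, 4.0, 4.5, 5.0, 5.5 and 6.0 (sum 28.5). Term mean = (8 × 3.0 + 28.5)/14 = 3.75. Offset = 0.75 days.
- B. Scan at 40+0, or on the day of birth if later; preterm at 40+0. Offset = (1+2+3+4+5+6)/14 = 1.5 days, with a maximum of 6.
- C. Term scan at the later of 40+0 and birth + 7 days; preterm at 40+0. Offset = (0+1+…+13)/14 = 6.5 days.
- D. As C with 14 days. Offset = 13.5 days.

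**Bias = slope × offset/7.**

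| Scenario | Offset (days) | 1% per week | 3% per week |
|---|---|---|---|
| A | 0.75 | 0.11% | 0.32% |
| B | 1.5 | 0.21% | 0.64% |
| C | 6.5 | 0.93% | 2.79% |
| D | 13.5 | 1.93% | 5.79% |

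Over a wider assumed slope of 0.5–5% per week, B gives 0.1–1.1%, C 0.5–4.6% and D 1.0–9.6%. To produce the whole 16.7% gap, the slope would have to be 16.7/(offset/7): about 78% per week in B, 18% in C and 8.6% in D.

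**Effect on a two-sided 5% test (level assumed).** With 25% scan failure, 15 term and 60 preterm infants remain (20 × 0.75 and 80 × 0.75). The noncentrality is (0.10 × bias)/(SD × √(1/15 + 1/60)). The error rate depends heavily on the SD. The article prints 0.1, which at an assumed 13 per group gives t = 0.51 and does not fit the stated significance. An SD of about 0.025 is the largest that would. False-positive rates at 1–3% per week:

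| SD | B | C | D |
|---|---|---|---|
| 0.01 (assumed) | 5.1–5.6% | 6–16% | 10–51% |
| 0.025 | – | 5–7% | 6–12% |
| 0.1 (printed) | 5% | 5% | 5% |

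**The case against.** **The scan rule need not be contradictory.** A reader might infer that the article requires the impossible. But the inclusion criteria describe the term group as "healthy term infants at 39–40 weeks’ gestation from low-risk pregnancies delivered at CCDHB", which elsewhere is 39+0–40+6. Week 40 can therefore mean 40+0 to 40+6, and every term infant could then be scanned in time, although one born at 40+6 only on that day. This stands: the time point is loosely fixed, not contradictory. A window in days may well be in the full protocol, and its absence from an article is not a finding.

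**No passage says that term infants will be scanned later.** A reader might infer that late term scans would create the expected deficit by themselves. The documents do not support that. They give no birth-to-scan lag and no slope. Late preterm scans would push the other way, and timing as written gives 0.1–0.6% against 17%. Even scenario D at 3% per week is 5.79/16.7, about a third of the reference effect, and it puts term infants well outside the stated scan week.

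**Plasma and urine.** A reader might extend the same directional bias to these measures. The article reports a rise for cerebral creatine only, so no direction is shown for them.

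**Outcomes are called mainly descriptive, and adjustment may add little.** With a common window that is kept, adjustment changes little. Without one, age at scan is nearly confounded with term status. Both are fair. They argue for doing both things and for showing the age distribution. They do not argue for leaving a named primary comparison unadjusted for a variable known from birth and scan dates.

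**Conclusion.** The point holds in a conditional form. The article fixes an unadjusted two-sample test for a measure that it describes as rising with age, and its recruitment range can delay scans in the term group only. If term infants are older at scan on average, part of an apparent preterm deficit will be an age effect.

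The size is about 0.1–0.6% if scans occur at or near birth within week 40. It is about 1–6% with assumed lags of 7–14 days and preterm scans at 40+0. Both ranges assume uniform births and a rise of 1–3% per week. Confidence is moderate: the structure of the problem is in the text, but the inputs that set its size are not.

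**What to change.** 1. Record postmenstrual age at scan for every infant. It follows from the birth and scan dates.
2. Aim for one scan window, stated in days, that all five groups can meet.
3. Replace the t-test or Mann-Whitney test for cerebral creatine with a linear model on gestational group (four preterm groups against term) and postmenstrual age at scan. Report the pooled preterm–term contrast from that model.
4. Show the distribution of age at scan by group, so that readers can judge the overlap.

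This needs changes of wording and one extra recorded variable. The model uses a few degrees of freedom. If ages at scan barely overlap between term and preterm infants, the adjusted contrast rests on extrapolation and should be reported as such, which is why the common window matters as much as the model.
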